## Abstract

**Background:**

The energy metabolism of drug-resistant tumor cells can provide a survival advantage during therapy, and treatment itself may influence metabolic reprogramming. *Petiveria alliacea* (Traditional name: Anamu*)* could inhibit glycolysis and OXPHOX modulating tumor metabolism, making it a potential treatment for tumors with altered metabolism. This clinical study aims to evaluate the safety and efficacy of a standardized Anamu phytomedicine called Esperanza in treating gastric tumors and acute leukemias.

**Methods:**

This is a prospective, open label, phase I/ randomized, double-blind single-center phase II study designed to evaluate the safety and efficacy of Esperanza extract in patients with metastatic gastrointestinal tumors and acute leukemias. In stage 1, the study will determine the MTD and assess safety. In stage 2, safety at the MTD will be evaluated, and the efficacy of Esperanza extract will be explored in both metastatic gastric tumors and acute leukemias. Quality of life improvement will be the primary outcome in the gastric tumor group, while different efficacy outcomes will be assessed in the acute leukemia group. A placebo group will be used for comparison in the gastric tumor group, and a historical control group will be used in the acute leukemia arm.

**Discussion:**

This clinical trial aims to evaluate the safety profile of the Esperanza extract in patients with metastatic gastrointestinal tumors and acute leukemias, while exploring its potential efficacy in conjunction with standard treatment for these pathologies.

**Trial registration:**

This trial was registered in the US National Library of Medicine with identifier NCT05587088. Registered October 19^th^, 2022.

**Supplementary Information:**

The online version contains supplementary material available at 10.1186/s12906-023-04109-2.

Role of sponsor {5c}	This clinical trial is part of the GAT Program – Scientific Ecosystem, which is headed by [name]. [name]. The ecosystem is focused on developing therapeutic options from plant-based sources that comply with FDA regulatory standards. The trial specifically aims to advance the development of Anamu phytomedicine and is spearheaded by [name]. [name]. The clinical study is being conducted exclusively at the Centro Javeriano de Oncología at the Hospital Universitario San Ignacio

## Introduction

### Background and rationale {6a}

The development of drug-resistant tumor cells is a major challenge in cancer treatment. Tumor cells with altered energy metabolism may have an advantage during adaptation to therapy, and the type of therapy can influence metabolic reprogramming [1, 2]. This means that attacking a single molecular target or metabolic pathway may favor the selection of chemotherapy-resistant clones [3]. Additionally, traditional cancer treatments may not necessarily reduce metastasis. Metastatic colonization requires an increase in adenosine triphosphate (ATP) production and a metabolic "rewiring" that reduces the production of reactive oxygen species (ROS) and redirects the toxic radical scavenging capacity to the mitochondria, making antioxidant defenses important for favoring metastasis [4].

Considering the significant intratumoral metabolic heterogeneity and plasticity observed in tumors, it is improbable that single agents will prove effective as a cancer treatment. Instead, combined therapies that simultaneously target two or more metabolic pathways can effectively impede relapse and the emergence of resistance. For instance, the complete eradication of tumor stem cells (TMCs) within the tumor can be achieved by dual inhibition of the primary metabolic pathway and its key escape mechanism. Such results have been documented in studies combining metformin with the bromodomain and extra-terminal (BET) inhibitor, JQ-1, in pancreatic cancer [5], as well as through phosphatidylinositol-3-kinase (PI3K) inhibition in ovarian cancer [6]. These combinations block oxidative phosphorylation (OXPHOS) and indirectly inhibit glycolysis simultaneously. Current understanding underscores the significance of meticulously designed therapies that target metabolically diverse populations and account for the tumor microenvironment. These considerations are paramount in developing more effective treatment strategies focused on metabolism [7].

Traditional Chinese medicine (TCM) has been used for thousands of years and has become a treatment option in many cancer centers worldwide [8]. TCM and some traditionally used plants interfere with cancer metabolism through various pathways and targets, including glycolysis and fatty acid synthesis [9]. The altered metabolism also negatively affects the activation of the immune response, so antitumor treatment focused on metabolic dysfunction may allow for better activity of the immune response and better response to biological therapies with antibodies against immune response checkpoints.

In Colombia, there is a significant collection of medicinal plants used by indigenous communities, some of which also coexist in other regions of the world. *P.alliacea* (*Petiveria alliacea*) is one such plant, which has shown enormous therapeutic potential in various ethnopharmacological studies [10–12]. Methanolic extracts of *P.alliacea* have exhibited cytotoxic activity on various cancer cell lines, including hepatocellular carcinoma cells, melanoma cells, leukemia cells, breast cancer cells, and colon cancer cells [13]. The whole plant decoction has been shown to be an immunostimulant, activating murine splenocytes and stimulating the production of interferon and interleukins 4 and 2, as well as increasing the activity of natural killer cells [14]. Hexanolic extract of *P.alliacea* has been shown to increase the phagocytic index of human granulocytes, and hydroalcoholic extracts have demonstrated immunomodulatory activity by increasing phagocytosis and activating NK cells with increased IL-2 and IFNg production. In contrast, anti-inflammatory activities have been seen in other experimental models, where the extract decreased the formation of granulomas and dermatitis in rodents previously treated with proinflammatory agents [15, 16].

In our group, we have identified several activities of the *P.alliacea* extracts that affect tumor metabolism. Notably, the extract can modulate various proteins associated with cell metabolism, including peroxiredoxin 6, glucose phosphate isomerase, ACLY variant protein, phosphoglycerate dehydrogenase, pyruvate kinase, enolase 1, fatty acid synthase, lactate dehydrogenase A, phosphoglycerate kinase (PGK), ATP synthase-H transporter, mitochondrial F1 complex, glyceraldehyde-3-phosphate dehydrogenase, glucosidase II, prostaglandin E synthase 3 (cytosolic), and dihydropyrimidinase variant type 2. Furthermore, chaperone proteins such as Hsp70, Hsp60, tumor rejection antigen (gp96), Heat Shock Proteins 90 (Hsp90), and Hsp90alpha were downregulated after extract treatment. These proteins are crucial for cell survival and protection against stressful stimuli, highlighting the extract's potential as an effective therapeutic agent against cancer [17]. The *P.alliacea* extract has demonstrated specific cytotoxic activity against various breast cancer cell lines, while sparing fibroblasts and normal epithelial cells. It has also been found to reduce glycolytic flux early, leading to a decrease in mitochondrial β-F1-ATPase and a marked reduction in mitochondrial ATP levels. These metabolic alterations correlate with reduced spheroid formation and proliferation capacity of 4T1 cells in vitro, as well as decreased tumor size in TS/A murine breast cancer tumor cell transplants [18, 19]. Our group has also shown that the aqueous fraction of *P. alliacea* induces partial maturation of human dendritic cells and the production of pro- and anti-inflammatory cytokines, while the organic fraction does not have immunomodulatory activity. These findings suggest that the antitumor effects of the aqueous extract of *P. alliacea* occur through various mechanisms, including the regulation of tumor metabolism, reduction of inflammation, and modulation of the immune response [20]. Additionally, the Anamu extract, which does not exhibit significant antioxidant activity, induces the death of blasts from patients with Acute Lymphoid Leukemia and a greater proportion of Acute Myeloid Leukemia, especially those from relapsed patients, as demonstrated in primary leukemia cell analysis [21].

Despite the significant amount of research done on *P. alliacea,* more controlled clinical studies are needed to validate its therapeutic potential in cancer.

### Objectives {7}

The main goal of phase I is to assess the safety, toxicity, and maximum tolerated dose (MTD) of the Esperanza extract in patients diagnosed with metastatic gastric tumors and acute leukemias. In phase II, the focus shifts to evaluating the safety of the extract and examining its impact on improving patients' quality of life using the QLQ-C30 scale for gastric tumors. Additionally, in the context of acute leukemias during phase II, the emphasis remains on determining the safety of the extract and investigating its potential to enhance the rate of remission during induction therapy and/or facilitate hematological recovery.

In addition to the primary objectives, there are important secondary objectives for gastric tumors. One of these is to evaluate the influence of the Esperanza extract on progression-free survival and clinical response, which will be assessed using the RECIST 1.1 criteria. For acute leukemias, the assessment will focus on event-free survival, defined as the duration from enrolment to disease progression, including local or distant recurrence, second primary malignancy, primary malignancy-related death, or death from any cause, whichever comes first. Furthermore, a thorough evaluation of the impact on patients' quality of life will also be conducted.

### Trial design {8}

This is a comprehensive phase I/II clinical study designed to assess both the safety and efficacy of the Esperanza extract in treating gastric tumors and acute leukemias. The study consists of two phases: Phase I is an open-label study that involves dose escalation to determine the MTD of the extract (Fig. 1). In Phase II, specifically for gastric tumors, a double-blind, randomized, placebo-controlled approach will be employed. Participants will be divided into two groups, with both groups receiving standard chemotherapy in combination with either the Esperanza phytomedicine or a placebo (Fig. 2a).

**Fig. 1 Fig1:**
[figure not shown]
Flow diagram for phase I in gastrointestinal tumors and acute leukemias

**Fig. 2 Fig2:**
[figure not shown]
Comprehensive Flow Diagram for Phase II PA001 Trial **a**) Gastrointestinal Tumors, **b**) New diagnosis Acute Leukemias, and **c**) Relapsed Acute Leukemias

Conversely, in the acute leukemia group, the MTD will be administered to patients during the induction cycle. The results from these acute leukemia cohorts will be compared to a historical cohort at the hospital, allowing for further analysis and evaluation (Fig. 2b). In relapse acute leukemia patients, the MTD will be administered to patients during the rescue cycles 1 to 3, the results will be compared to a historical cohort at the hospital (Fig. 2c).

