**Efficacy Assessment**					
RECIST		X			X
Tumor Antigens		X			X
CA199		X			X
ACE		X			X
Metabolome		X		X	X
Microbiome Analysis		X			X
Proinflammatory Cytokines		X		X	X
Circulating DNA		X		X	X
Ketone Bodies		X		X	X
Tumor Infiltration		X			X
QLQ C-30 Quality of Life Surveys		X	X	X	X
Progression-Free Survival		X			X

For newly diagnosed acute leukemias, a total of 28 new patients will be recruited, and an additional six patients will be recruited for the relapsed leukemias group. Both groups will receive continuous treatment with the Esperanza extract at the determined MTD for four weeks. Standard chemotherapy treatment for their underlying disease will be administered to both groups. At the end of the treatment cycle, safety and efficacy evaluations will be conducted. Table 3 provides a comprehensive list of the activities to be carried out during the patients' intervention.

**Table 3 Tab3:** Activity schedule for phase II clinical trial in acute leukemias

Schedule of activities				

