**Interventions**				
Medication dispensing		**X**	**X**	**X**
Follow-up visit		**X**	**X**	**X**

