**Efficacy Assessment**				
Myelogram and flow cytometry		X		X
Tumor Antigens		X		X
Metabolome		X		X
Microbiome Analysis		X		X
Proinflammatory Cytokines		X		X
Circulating DNA		X		X
Ketone Bodies		X		X
Tumor Infiltration		X		X
QLQ C-30 Quality of Life Surveys		X	X	X
Progression-Free Survival		X		X

^a^For new diagnosis the intervention will be only in induction chemotherapy cycle with the close out visit in week 6

The Esperanza and Placebo capsules will be manufactured at Labfarve Laboratories in strict adherence to Good Manufacturing Practices (GMP) conditions. The Esperanza capsules contain 500 mg of *P. alliacea* extract, which is obtained from freshly crushed leaves infused with purified water. The extraction process has a DER (Drug extraction ratio) of 29–44:1, and the hexose content ranges between 3.0% and 5.0%. Each batch undergoes chemical profile assessment to ensure consistency. Quality controls are conducted in accordance with regulations set forth by the World Health Organization (WHO), the National Institute for Food and Drug Surveillance (INVIMA), and the U.S. Food and Drug Administration (FDA). These controls will be applied to both the investigational phytomedicine and the placebo, guaranteeing an identical physical appearance and a shelf life of six months from the date of manufacture.

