### Outcomes {12}

The primary outcome of this study is to determine the safety, efficacy, and maximum tolerated dose (MTD) of the administration of the Esperanza extract in patients with metastatic gastrointestinal tumors as well as in patients with acute leukemias. Additionally, the study aims to assess the impact of the Esperanza extract on the quality of life of these patients using the QLQ-C30 scale. The evaluation period will be between 4 and 6 months, and the QLQ-C30 version 3 scale will be employed as the standardized method for assessing the patients' quality of life outcomes.

The secondary outcomes of this study are as follows:To determine the effect of treatment with the Esperanza extract in combination with chemotherapy on the clinical and pathological response. This evaluation will be conducted between 1 and 3 months using the Recist 1.1 (Response Evaluation Criteria In Solid Tumors) scale as the standardized evaluation method and with flow cytometry and myelogram in acute leukemias.To assess the impact of treatment with the Esperanza extract in combination with chemotherapy on the number and size of metastases. This assessment will also be carried out between 1 and 6 months, utilizing the Recist 1.1 for gastrointestinal tumors and cytometry and myelogram for acute leukemias.To determine progression-free survival and overall survival. The evaluation period for progression-free survival will be 3 months, and the Log Rank test will be used as the evaluation method. Progression-free survival will be measured from randomization to the occurrence of disease progression, local or distant recurrence, development of a second primary malignancy, or death from any cause, whichever occurs first. Patients who do not meet the evaluation time point will be censored and followed up until the end of treatment for survival curve preparation.

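### For relapsed acute leukaemia in phase II, the protocol gives conflicting extract exposure periods and conflicting times of response assessment

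*Protocol article*

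**What the plan says.** Four places in the protocol article bear on relapsed acute leukaemia in phase II.

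- **Trial design {8}**, in the text after Fig. 2: "In relapse acute leukemia patients, the MTD will be administered to patients during the rescue cycles 1 to 3". Results are to be compared with a historical cohort at the hospital.
- **Intervention description {11a}, Phase II treatment.** After naming 28 newly diagnosed patients, it adds that "an additional six patients will be recruited for the relapsed leukemias group". It continues: "Both groups will receive continuous treatment with the Esperanza extract at the determined MTD for four weeks". On timing it says: "At the end of the treatment cycle, safety and efficacy evaluations will be conducted".
- **Table 3**, headed for acute leukaemias in general. Cycle 1 is at Week 2, cycle 2 at Week 6 and close-out at Week 10. The row "Myelogram and flow cytometry" is marked at the initial visit and at close-out only, as are the laboratory tests, electrocardiogram and echocardiogram. The row "Medication dispensing" is marked at Week 2, Week 6 and close-out. The footnote reads: "For new diagnosis the intervention will be only in induction chemotherapy cycle with the close out visit in week 6". It makes no exception for relapsed patients.
- **Outcomes {12}**, on clinical and pathological response: "This evaluation will be conducted between 1 and 3 months using the Recist 1.1", with flow cytometry and myelogram named for the leukaemias. This is a window, not a fixed time.

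**The concern.** The first two statements conflict on their face, and Table 3 fits neither. Followed as written, they give site staff different times to stop dispensing and different times to examine the marrow in the same patients.

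Two things depend on the answer. The first is the endpoint. Response after one, two or three rescue cycles is a different quantity in each case, and this group is judged against historical records. Sequence generation {16a} plans propensity score matching for the leukaemia comparison. Matching on patient characteristics does not by itself ensure that trial patients and controls are read after the same number of cycles.

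The second is safety observation. Table 3 has no column after Week 10, so a third cycle on its spacing would have no scheduled laboratory test, electrocardiogram or marrow assessment.

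**Working it through.** The plan gives no figure to reproduce. The check sets the statements side by side and converts them to weeks.

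**Inputs**
- Start of treatment: Week 2 (Table 3).
- Cycle length L: not stated for rescue cycles. Table 3 places cycles 1 and 2 four weeks apart, and the gastrointestinal arm equates three cycles with about 12 weeks. I therefore assume L = 4 weeks.
- Response is taken to be read at the end of exposure, as the Phase II treatment section describes.

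**Formulas for k cycles:** exposure = k × L; end of exposure = Week 2 + k × L.

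| Source | k | Exposure | End of exposure and response reading |
|---|---|---|---|
| Phase II treatment | 1 | 4 weeks (stated) | 2 + 4 = Week 6 |
| Table 3 with its footnote | 2 (inferred) | 2 × 4 = 8 weeks | 2 + 8 = Week 10 |
| Trial design | 3 | 3 × 4 = 12 weeks | 2 + 12 = Week 14 |

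The longest exposure is 12 / 4 = 3 times the shortest. The latest reading falls 14 − 10 = 4 weeks after the last column of Table 3.

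**Dependence on L.** Three cycles fit into the stated four weeks only if 3L = 4, so L is about 1.3 weeks. They fit by Week 10 only if 3L ≤ 8, so L is at most about 2.7 weeks. Neither matches the four-week spacing in Table 3. The exact week figures rest on L = 4, but the conflict does not.

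**Alternative readings of the Trial design sentence**
- All three rescue cycles: conflicts with four weeks and with Week 10.
- Up to three cycles, varying by patient: conflicts with a fixed four weeks.
- Whichever rescue cycle the patient is in at entry: agrees with four weeks, but leaves four weeks in conflict with cycle 2 and the Week 10 close-out in Table 3.

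**Outcomes window.** One to three months is wide enough to take in, roughly, all three times, so it does not settle the matter.

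**Newly diagnosed group.** One induction cycle from Week 2 plus 4 weeks ends at Week 6. Trial design, Phase II treatment and the Table 3 footnote agree on this, so the inconsistency is confined to relapsed patients.

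**The case against.** The strongest reply is that only the Phase II treatment section states a duration in weeks. Table 3 is a shared visit schedule and never says how long relapsed patients take the extract. Its dispensing mark at close-out is weak evidence, because Tables 1 and 2 carry the same mark. The Trial design sentence is open to more than one reading, and Fig. 2c, drawn for this group, is not visible here. Much of this stands: the two-cycle schedule is an inference, and the figure may show what is intended. It does not remove the conflict, because each reading of the Trial design sentence leaves at least two places in disagreement. The footnote, by exempting only newly diagnosed patients, leaves cycle 2 and Week 10 to the relapsed group. A condensed article may omit detail, but these are conflicting statements.

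A reader might also infer more than the documents support:

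- *That response timing is undefined.* Table 3 does give a close-out time. The timing is inconsistently defined.
- *That remission will be inflated against the historical cohort.* This would require controls to be read after fewer cycles, and nothing says so. That detail may be in the full protocol or analysis plan, which are not shown. Sizing such a bias would need a per-cycle remission rate, which the documents do not give.
- *That the conflict is what takes exposure beyond phase I.* Phase I lasts 8 weeks, and the gastrointestinal arm already plans about 12 weeks at the MTD. Longer exposure than in phase I is an open feature of the design, and reconciling these passages would not change it.
- *That the whole leukaemia comparison is compromised.* The newly diagnosed schedule is consistent.

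**Conclusion.** The point holds as an internal inconsistency. For relapsed acute leukaemia in phase II, neither the exposure period nor the response time point can be fixed from the text. The clash between rescue cycles 1 to 3 and four weeks is explicit; the two-cycle, Week 10 schedule is inferred from Table 3 and its footnote. With cycles of about 4 weeks, exposure runs from about 4 to 12 weeks and response assessment from Week 6 to about Week 14. The 12-week and Week 14 figures rest on that assumed length.

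The correction is important but of limited reach. It concerns six of the 28 + 6 = 34 phase II leukaemia patients named in the Phase II treatment section and leaves the comparison in newly diagnosed patients untouched.

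**What to change.** - Reconcile Trial design {8}, the Phase II treatment section and Table 3 with its footnote, so that all give one exposure period and one response time point for relapsed patients. Fig. 2c should be checked against the result. Which period applies is for the sponsor to decide.
- Align the scheduled dispensing, safety tests and marrow assessments in Table 3 with that period, preferably in a separate column set or footnote for relapsed patients.
- State that response in the historical relapsed controls is read after the same number of rescue cycles as in trial patients.

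The cost is amendment wording in these places, with no extra patients. If the period chosen runs past Week 10, the schedule for the six relapsed patients would also need to extend past its present last visit.

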## Methods: Participants, interventions, and outcomes

### Study setting {9}

This study aims to assess the safety and investigate the efficacy of the Esperanza extract in treating gastric tumors and acute leukemias. The research will be exclusively conducted at the Hospital Universitario San Ignacio. During Phase I, the safety profile of the extract will be evaluated when used in combination with standard chemotherapy for each specific tumor type. In Phase II, the focus will shift to exploring the extract's efficacy while continuing to assess its safety.

